## e) Equipment to be used for assessing the clinical investigation variables

### Functional performance testing

Functional balance will be examined. Table 2 lists the different tests. A 6-min walking test, dual-task L-test, L-test, slope walking test, and stairs climbing and descending test will indicate functional balance and dual-task performance. Rating of perceived exertion [16], level of fatigue and comfort [17] and NASA-Task Load index (NASA-TLX) assessing perceived workload [18] will be assessed after each task.

| Performance tests                       | Outcome                       | Materials                   |
|-----------------------------------------|-------------------------------|-----------------------------|
| Slope walking test [19]                 | Time to complete test         | Stopwatch                   |
|                                         | Biomechanical gait parameters | Inertial measurements units |
| Stair climbing and descending test [20] | Time to complete test         | Stopwatch                   |
|                                         | Biomechanical gait parameters | Inertial measurements units |
| Dual-task L-test [21]                   | Time to complete test         | Stopwatch                   |
|                                         | Accuracy of subtractions      | Audio-recorder              |
| L-test [21]                             | Time to complete test         | Stopwatch                   |
| 6-min walking test [5]                  | Distance covered in 6 minutes | Measuring wheel             |
|                                         | Biomechanical gait parameters | Inertial measurements units |

Table 2: Physical performance tests

The primary endpoint is the distance covered during the 6-min walking test. Any difference found between the different prostheses on the distance travelled will be considered clinically relevant from a difference of 35 metres [5]. Secondary endpoints will comprise performance on the L-test, dual-L-test, slope walking test and stairs climbing and descending test, and the evaluation of the gait pattern.

Initial measurements units (Awinda, Xsens Technologies B.V., Enschede, The Netherlands) will be capturing 3D-accelerations and angular velocities during the 6-min walking test, the slope walking test and the stairs climbing and descending test to evaluate the participants' gait pattern [22]. The data of the inertial measurement units will be used to evaluate coordination patterns between joints or segments based on continuous relative phase plots. We opt to evaluate this, as high variability in the gait pattern increases the risk of falling. Biomechanical data will be analysed and purified using Matlab (The MathWorks Inc., Massachusetts, United States).

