### b) Objectives

The different research objectives (ROs) are:

**RO.1.1** The primary aim is to investigate the effect of walking performance with a new passive ankle device (LUNARIS®) compared to the current prosthetic ankle device in people with a unilateral lower limb amputation.

**RO.1.2** A second aim is to examine the effect of the different prostheses on postural stability in people with a unilateral lower limb amputation.

**RO.1.3** A third aim is to determine if the type of prosthesis changes the movement pattern during walking in an individual with a unilateral lower limb amputation.

**RO.2** The secondary aim is to examine changes in whole-brain networks related to the type of prosthesis in people with a unilateral lower limb amputation by means of MRI and diffusion tensor imaging.

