### d) Primary and secondary hypotheses

The different hypotheses (H) are:

**H1** We hypothesise that people walking with the passive prosthesis (LUNARIS®) will be able to cover significantly more distance (i.e.,  $> 35$ m) during 6-min walking compared to people walking with their current prosthetic device [4][5]. Secondly, we expect that wearing the LUNARIS® will improve postural stability and improve movement patterns after 12 weeks compared to walking with the current ankle prosthesis [6][7][8]. Thirdly, we noticed based on anecdotal evidence that people walking with the LUNARIS® are able to descend stairs more naturally, like able-bodied people. We hypothesise that doing the rehabilitation with the LUNARIS® will help people descending stairs without the need of rolling over the edge of a step, and as a consequence, will reduce the number of falls.

**H2** Based on my literature review on brain neuroplasticity after a lower limb amputation, we hypothesise to discover differences in structural whole-brain networks between participants with the LUNARIS® and current prosthesis after 12 weeks. We assume that these differences in structural networks will be less pronounced among people wearing the LUNARIS® compared to people wearing the current

prostheses [9]. Furthermore, we expect that these disparities in brain structural connectivity will translate into a change in performance on the physical tests.

e) Risks and anticipated adverse device effects that are to be assessed

To date, no device deficiencies have been reported with the LUNARIS®. We are not yet able to give a concise summary of device deficiencies and thus not able to report any deficiency that might have led to a serious adverse event if appropriate action had not been taken, intervention had not occurred, or circumstances had been less fortunate.

The Risk Management File is attached to this document.

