### b) Descriptive statistics of baseline data

#### *Functional performance testing*

A mixed model will be constructed enabling within and between group (i.e., type of prosthesis) comparison of balance performance and accounting for baseline covariates. If residuals are not normally distributed, required adaptations to the data or model will be performed. To correct for multiple comparisons, suited corrections will be applied. The factors age, time since amputation, side of amputation, level of amputation, time using prosthesis, previously used prosthesis will be accounted for. Statistical significance level will be set at 5%.

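### RO.1.2 and H1 promise a result on postural stability, but no outcome or declared endpoint is assigned to it, and the walking tests are labelled as balance in its place

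*Protocol*

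**What the plan says.** Section 5 b) lists separate aims. RO.1.1 concerns walking performance. RO.1.2 reads: "A second aim is to examine the effect of the different prostheses on postural stability in people with a unilateral lower limb amputation". RO.1.3 reads: "A third aim is to determine if the type of prosthesis changes the movement pattern during walking". In section 5 d), H1 again names stability and movement as two effects: "we expect that wearing the LUNARIS® will improve postural stability and improve movement patterns after 12 weeks".

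Section 6.1 e) describes the tests. The sentence that lists all five (6-minute walk, dual-task L-test, L-test, slope, stairs) ends: "slope walking test, and stairs climbing and descending test will indicate functional balance and dual-task performance". Table 2 gives the outcome of each test. The primary endpoint is 6-minute walk distance. The statement on the other endpoints is: "Secondary endpoints will comprise performance on the L-test, dual-L-test, slope walking test and stairs climbing and descending test, and the evaluation of the gait pattern". The paragraph after Table 2 says that the inertial units serve to evaluate the gait pattern, through coordination between joints or segments. Its reason is that high gait variability raises the risk of falling.

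Section 7 b) describes the mixed model for functional testing as enabling a "comparison of balance performance and accounting for baseline covariates".

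**The concern.** Three terms are used without a link between them: postural stability in the objective and hypothesis, functional balance in the description of the tests, and balance performance in the analysis. If they mean the same thing, the evidence for RO.1.2 is the set of walking-test scores. If they do not, RO.1.2 has no evidence assigned to it.

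Time to complete a course and distance in six minutes are speed-type scores. The same score can come from a steady or an unsteady gait, so a difference between prosthesis groups in seconds or metres cannot be attributed to stability rather than to speed. At stake is whether the second part of H1 can be answered at all by what the Protocol says will be measured.

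**Working it through.** No sample size, power or significance level bears on this point. The check maps objectives to outcomes and then to the analysis.

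**Step 1: outcomes in Table 2**

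| Test | Time | Distance | Subtraction accuracy | Inertial gait parameters |
|---|---|---|---|---|
| Slope | 1 | – | – | 1 |
| Stairs | 1 | – | – | 1 |
| Dual-task L-test | 1 | – | 1 | – |
| L-test | 1 | – | – | – |
| 6-minute walk | – | 1 | – | 1 |
| Total | 4 | 1 | 1 | 3 |

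4 + 1 + 1 + 3 = 9 rows. Every test has a time or distance score. Three of five add inertial data and one of five adds a cognitive score. Rows labelled as stability, sway or standing balance: 0 of 9.

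**Step 2: declared endpoints.** There is one primary (distance). The secondary endpoints are performance on four tests plus the gait pattern. None is named as postural stability.

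**Step 3: other instruments.** Perceived exertion, fatigue, comfort and workload are rated after each task. The PEQ is described as measuring quality of life, QUEST 2.0 as measuring satisfaction and the Mini-Mental State Examination as covering cognition. None is presented as a stability measure.

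**Step 4: objectives against outcomes**

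| Objective | Outcome that the text supports |
|---|---|
| RO.1.1 walking performance | 6-minute walk distance; timed tests |
| RO.1.2 postural stability | none named |
| RO.1.3 movement pattern | inertial data: gait pattern, coordination |
| RO.2 brain networks | MRI |

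The Protocol does not print this mapping. It follows from matching the wording of each objective to the stated purpose of each measurement. One of four objectives is left without an outcome.

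**Step 5: what could fill the gap as written.** There are two candidates.

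- The time and distance scores, through the functional-balance and balance-performance labels. These overlap with RO.1.1.
- The coordination data, through their fall-risk rationale. These are the RO.1.3 outcome.

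Neither is defined as postural stability.

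**Step 6: consequence for a speed adjustment.** Mean speed in the 6-minute walk is distance / 360 s, so it is the primary endpoint on another scale. The 35 m threshold equals 35 / 360 ≈ 0.10 m/s. H1 expects the device to change distance by more than that, and speed is measured after allocation. Adjusting a stability outcome for it would remove part of the device effect being estimated.

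**The case against.** The strongest reply is that the inertial data already carry a stability rationale, since the coordination analysis is justified by the risk of falling. A gait-variability parameter is close to what RO.1.2 needs, and an SAP, which is not at hand, could specify it. This stands in part: the raw signal for a stability measure is being collected, and it would be wrong to say that nothing relevant is recorded. But the Protocol directs those data to gait pattern and never links them to postural stability. An SAP that named a stability parameter would still sit beside a Protocol that attaches balance to the walking tests.

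A second reply is that timed mobility tests may be accepted indicators of functional balance. That depends on the sources cited for the tests, which were not available, so this point does not claim that the tests are invalid. It claims only that the Protocol promises postural stability apart from walking performance and gives no argument that time or distance isolates it.

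A reader might infer that a faster walk will be reported as better balance, or that one gain will be counted under both RO.1.1 and RO.1.2. The documents do not support that. No reporting rule says so, the term balance performance is left undefined, and the timed tests are declared as endpoints distinct from distance.

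**Conclusion.** The point holds in this form: RO.1.2 and the stability part of H1 have no assigned outcome and no declared endpoint (0 of 9 rows in Table 2; one of four objectives), while the walking tests carry balance labels that their time, distance and accuracy scores do not support on their own. As written, a conclusion on postural stability would rest on speed-type scores or on the RO.1.3 outcome.

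This is more than missing analysis detail, because it concerns which measurement answers a stated objective. It should be corrected, but it is limited to a non-primary objective: the 6-minute walk distance, its 35 m threshold and the sample size are untouched. The conclusion assumes that the inertial data belong to RO.1.3, as their stated purpose indicates. It does not extend to saying that stability cannot be measured in this trial.

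**What to change.** Choose one of two changes.

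1. **Name an endpoint.** In Table 2 and the endpoint statement, define one stability parameter from the inertial data already recorded in the 6-minute walk as the RO.1.2 secondary endpoint, at weeks 12 and 24. Examples are the root mean square of mediolateral trunk or pelvis acceleration, or stride-time variability. The first assumes a sensor at the trunk or pelvis; the Protocol does not state sensor placement. Make the group comparison without adjustment for walking speed the main one, and show a speed-adjusted version only as supportive. State in section 7 b) which outcome balance performance refers to.

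2. **Narrow the claim.** Reword RO.1.2, H1, the test description in section 6.1 e) and section 7 b) to functional mobility, and draw no postural-stability conclusion from the timed tests.

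The first costs one more secondary outcome and some data processing, with no new visit or equipment. The second costs a few sentences and gives up the stability claim.

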##### Protocol:

Figure 2 provides a visualisation of the investigation workflow.

[figure not shown]

Figure 2: Overview clinical trial. MRI: Magnetic Resonance Imaging, PEQ: Prosthetic Evaluation Questionnaire, ADL: Activities of Daily Living

The clinical investigation will comprise 4 test days for participants with a lower limb amputation and 2 days for the control group of able-bodied individuals.

The able-bodied individuals will undergo an MRI-scan at the University hospital Brussels (dpt. Radiology and Magnetic Resonance) and then perform functional performance tests.

Participants with a lower limb amputation will start the clinical investigation upon the start of their rehabilitation. At week 0, when initiating the rehabilitation, participants will undergo a baseline MRI-scan at the University hospital Brussels (dpt. Radiology and Magnetic Resonance). Then, they will be allocated to the one of the treatment arms (LUNARIS® or the SACH® foot) and will conduct their rehabilitation to learn walking with a prosthesis. At the end of the rehabilitation, after 12 weeks, participants will perform baseline functional performance tests, fill out the prosthetic evaluation questionnaire (PEQ) measuring quality of life [11] and fill out the Mini-Mental State Examination to account for cognitive impairments and onset of Alzheimer's Disease [12]. Between weeks 12 and 24 of the clinical investigation (i.e. intervention period), participants will perform their daily activities with the allocated prosthesis. During this 12-week period, trying out new prosthetic devices will be allowed within the group of individuals wearing the SACH® foot as this is considered the usual care. At the end of this period (after week 24), post-test assessment will take place and participants will undergo the same MRI and functional performance tests as during the baseline assessments to evaluate the changes that occurred. Additionally, the participant will be asked to fill out the Quebec User Evaluation of Satisfaction with assistive Technology (QUEST 2.0) to assess prosthetic satisfaction [25-27]. The 12-week intervention period is chosen based on a study examining the effect of 12 weeks balance training in healthy and older adults on neuroplasticity and on the accommodation time to walking with a new prosthesis [13][14][15].

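### Raw dual-task L-test time, not contrasted with the plain L-test, cannot by itself support a statement about dual-task performance (minor; one secondary endpoint)

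*Protocol*

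**What the plan says.** Section 6.1 e) of the protocol (Functional performance testing) names two constructs for the set of five tests: the "stairs climbing and descending test will indicate functional balance and dual-task performance". Table 2 then lists the outcomes. The dual-task L-test has two rows, "Time to complete test" by stopwatch and "Accuracy of subtractions" by audio-recorder. The plain L-test has its own row with completion time only. No denominator or scoring rule is given for the accuracy.

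On status, "The primary endpoint is the distance covered during the 6-min walking test". For the rest, "Secondary endpoints will comprise performance on the L-test, dual-L-test, slope walking test and stairs climbing and descending test", together with the gait pattern. The plain and the dual-task L-test thus appear side by side as separate items.

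Section 7 b) gives the analysis: "A mixed model will be constructed enabling within and between group (i.e., type of prosthesis) comparison of balance performance". The named factors are these: "The factors age, time since amputation, side of amputation, level of amputation, time using prosthesis, previously used prosthesis will be accounted for". Plain L-test time is not among them, and no dual-versus-plain contrast, ratio or combined time-and-accuracy rule is stated.

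The functional tests are done at weeks 12 and 24. The first of these comes after 12 weeks on the allocated foot (section 6.1 d): "At the end of the rehabilitation, after 12 weeks, participants will perform baseline functional performance tests".

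**The concern.** The time to walk the L-test course while subtracting is made up of the time to walk the course and the extra time that the second task causes. Only the extra time speaks to dual-task performance. H1 expects people on the LUNARIS to walk more than 35 m further in six minutes, which means faster walking. If that speed carries over to the L-test course, both L-test times shorten together and the dual-task L-test will favour the LUNARIS with no change in the cost of the second task. One speed effect could then be reported twice, the second time under a dual-task label. The accuracy row does not settle this, because it is not tied to the time and its scoring is open.

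**Working it through.** The protocol states no figure for this endpoint, so there is none to reproduce. The check is a reading of Table 2, the endpoint list and section 7 b), followed by arithmetic. From the protocol come the 35 m, the 20 per arm and the 5% level. Everything else below is an assumption.

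**1. What a pure speed gain does.** Let S be plain time, D dual-task time and c the relative dual-task cost, so D = S(1 + c) and c = (D − S)/S. If walking becomes faster by a proportion s, then S′ = S(1 − s) and D′ = S(1 − s)(1 + c). Raw dual-task time falls by the proportion s. The cost and log(D/S) do not change.

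| Assumed case | Plain | Dual | Cost (D − S)/S |
|---|---|---|---|
| Before | 30 s | 40 s | 10/30 = 33% |
| After, 10% faster | 27 s | 36 s | 9/27 = 33% |

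Raw dual-task time improves by 4 s and the cost is the same. The same holds at S = 25 s and c = 20%: dual-task time goes from 30.0 s to 28.5 s (5% faster) or 27.0 s (10% faster), and the cost stays at 20%.

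**2. How often raw time would then be significant.** Assume 20 per arm, a two-sided t-test at one visit, plain time 30 s, mean cost 25% (dual-task time 37.5 s), log-SD of the cost 0.10, timing noise 0.05 on the log scale, and between-person log-SD of speed 0.10 to 0.25. A gain of 35 m on an assumed 350 to 450 m is a log difference of log(385/350) = 0.095 to log(485/450) = 0.075. At 400 m, dual-task time falls by 37.5 × (1 − 400/435) = 3.0 s. The SD of log raw time is √(speed² + 0.10² + 0.05²), which is 0.15 to 0.27. The noncentral t distribution gives significance for raw time in about 14% to 50% of trials. The log ratio has no true difference and is significant in 5%.

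**3. Precision if the cost really falls.** Take a fall from 25% to 15% with unchanged speed, a log difference of log(1.25/1.15) = 0.083. SDs at one visit are √(speed² + 0.10² + noise²) for raw time and √(0.10² + 2 × noise²) for the ratio. For change from week 12 to week 24 with stable cost, they are √(2 × noise² + 2 × visit-to-visit speed²) and √(4 × noise²).

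| Analysis and assumptions | Power, raw time | Power, ratio |
|---|---|---|
| One visit, noise 0.05, speed log-SD 0.25 to 0.10 | 16% to 40% | about 55% |
| One visit, noise 0.10, speed log-SD 0.10 | 32% | 32% |
| One visit, noise 0.15, speed log-SD 0.10 | 24% | 19% |
| Change, noise 0.05, speed stable between visits | 95% | 73% |
| Change, noise 0.05, visit-to-visit speed log-SD 0.05 | 73% | 73% |
| Change, noise 0.05, visit-to-visit speed log-SD 0.08 | 49% | 73% |

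The ordering depends on the noise and on whether change is analysed. The change rows also suppose that the effect arises between weeks 12 and 24. An effect complete by week 12 would not appear in the change.

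**4. The subtractions.** Suppose person A takes 40 s with 18 of 20 answers right, and person B takes 34 s with 6 of 6 right. As correct/attempted, B looks better (100% against 90%). As number correct, B looks worse (6 against 18). As correct answers per second, A has 18/40 = 0.45 and B has 6/34 = 0.18, so the neglected second task is visible.

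**The case against.** The best reply is that Table 2 lists what is measured and with what equipment, and does not fix a score. The plain L-test is collected at the same session, so a statistical analysis plan, which is not at hand, could derive the cost. Time to walk while subtracting is also a legitimate functional outcome in its own right, and the plain L-test result would be reported beside it. Dual-task benefit appears in no objective and no hypothesis. All of this stands, and it is why the point is minor. It does not remove the point: the protocol names dual-task performance as something the tests indicate, names the outcomes, and describes a model that neither contrasts nor adjusts the two times.

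Three stronger readings are tempting and are not supported.

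- A reader might infer that someone who gives up on the subtractions necessarily scores as better. That follows only if accuracy means correct/attempted. The protocol gives no denominator, and with number correct the neglect shows.
- A reader might infer that the ratio is always the more powerful measure. Step 3 shows that it can lead, tie or trail.
- A reader might take the 14% to 50% as a false-positive rate for the endpoint. It is not: in that scenario dual-task walking time really is shorter. It is the rate at which a speed effect could be mistaken for a dual-task effect.

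**Conclusion.** The point holds in a limited form. As listed, a difference between prostheses in raw dual-task L-test time cannot be attributed to dual-task ability, because a proportional gain in walking speed moves the raw time and leaves the dual-task cost where it was. That part is algebra and needs no assumed SD. It does rest on the speed gain acting in proportion on both times; if the second task added a fixed number of seconds, the relative cost would itself shift with speed. The frequency of about 14% to 50% against 5% rests on the assumed times, SDs and baseline distance, and on a single-visit test in place of the planned mixed model. It shows the possible scale and is not a forecast. One secondary endpoint is affected. The primary endpoint, the 6-minute walk distance, is untouched. Minor.

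**What to change.** In Table 2 and section 7 b):

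- Keep raw dual-task L-test time as a functional outcome.
- Add log(dual-task time / plain L-test time), both from the same visit, or equivalently a prosthesis-by-condition (plain/dual) term in the mixed model for log time. State that any dual-task benefit is claimed from this measure.
- Report correct subtractions per second (correct answers on the recording divided by stopwatch time) beside it, so that a time gain bought by dropping the second task can be seen.

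This takes about two sentences. Both times and the recording are already collected, so no test, visit or equipment is added. The downside is that the ratio carries the error of two timings and can be less precise than raw time. A cost for the subtraction task itself would need a subtraction-only condition, which the visits do not include and which is not asked for here.
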